#### Safety

As CDH is a condition already associated with a significant risk of complications, serious morbidity is often inherent to the disease and unrelated to the intervention that is under evaluation in this trial. Therefore, we have specified context-specific SAEs that are reported to the data and safety monitoring board (DSMB) and METC on an annual base and that are collected as secondary outcomes: oxygen dependency on day 28, sepsis, cerebral complications, and ECMO therapy. Non-context specific SAEs are reported to the METC within 15 days after the sponsor has first knowledge of the SAE. Postpartum haemorrhage (estimated maternal blood loss > 1000 ml) is considered a safety parameter, and the sponsor will as such report this serious adverse event (SAE) to the METC within 7 days of first knowledge.

A DSMB was established to advise the principal investigator in protecting trial safety. Members of this committee are two neonatologists, an obstetrician, and a statistician. As stated in the protocol, the DSMB will conduct two interim statistical analyses on safety during the course of this study, after approximately 25% and 50% of the total required patients have completed their primary outcome. Outcomes included in the interim analysis on safety include the abovementioned context-specific SAEs, neonatal mortality, and postpartum haemorrhage. The first interim analysis has been conducted and resulted in the DSMB advising in favour of continuing the trial.

### Statistical methods specified in the study protocol

#### Sample size calculation

As has been reported in the study protocol, the background incidence of pulmonary hypertension was previously reported at 69.7% in the first week after birth [9, 16]. Based on a suggested clinically relevant reduction in pulmonary hypertension incidence of one third, a total sample size of at least 140 infants was calculated with 80% power and a two-sided type I error of 5%.

#### Originally proposed analyses

After start of the trial, the initially proposed analysis plan was updated to increase feasibility of the study in all participating centres and to limit bias where possible. Here, we present our updated statistical analysis plan.

#### Interim analyses and safety reporting

As was specified in the study protocol, no interim analyses on efficacy will be performed. Only two interim analyses on safety are planned, after 25% and 50% of the total required patients have completed the primary outcome. The only stopping condition will be concerns regarding safety outcomes. The decision to terminate or continue the trial is advised by the DSMB. The interim safety analyses include SAEs and the pre-specified context-specific safety outcomes listed as exploratory outcomes. Before each interim analysis, the DSMB will receive a report that includes blinded data on safety outcomes. On request of the DSMB, treatment allocation can be unblinded. The first safety interim analysis, after 25% of the total required patients had completed the primary outcome, was performed in 2022. The DSMB advised to continue the trial based on this interim analysis. In the final report of the trial, a list of SAEs and reasons of mortality will be reported by allocation arm in supplementary tables. SAEs and context-specific safety outcomes will be reported as is described in the ‘Statistical analyses’ section on secondary outcomes.

### Statistical analysis plan

#### Overall principle

Statistical significance is set at *p* < 0.05, using two-sided tests. For all relevant outcomes, a 95% confidence interval (CI) will be reported. Statistical analyses will be performed using the computing environment R (R Core Team (2020), Vienna, Austria).

#### Data handling

Potential outliers will be investigated, and extreme outliers, defined as being more than three times the interquartile (IQR) range below the first quartile or above the third quartile, will be listed individually in a supplement to the main analysis. If it can be reasonably assumed that those extreme outliers are due to an error in the data, they will be excluded from all analyses. The data set will only be locked after completion of the data set, data cleaning, and data validation. The statistical analyses for significant differences are done on a blinded data set and will be carried out after locking the data set, which can only be reversed in case of exceptional circumstances and after agreement of the trial team that consists of the principal investigator, data managers, and the trial statistician.

#### Definition of analysis sets

The primary outcome will be analysed in a modified intention to-treat population to estimate the realised benefit of the intention to do PBCC over immediate cord clamping in patients with a prenatal diagnosis of CDH. The modified intention-to-treat population includes all patients that are randomised to a particular treatment arm (PBCC or immediate cord clamping), independent of actual treatment received, protocol deviations, or post-randomisation ineligibility. However, two exclusions apply: (1) patients without a confirmed prenatal diagnosis of CDH will be excluded from all analyses; (2) patients whose parents withdraw consent will be excluded from all analyses.

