#### Randomisation and data collection

Inclusion criteria and exclusion criteria are reported in detail in the study protocol [9]. Infants are eligible if diagnosed with an isolated left-sided CDH on prenatal ultrasound with gestational age at delivery ≥ 35.0 weeks [9]. Exclusion criteria are right-sided and bilateral CDH, antenatal diagnosed major associated structural or genetic abnormalities, high urgency caesarean section (intended interval to delivery < 15 min), cases that have been treated during pregnancy with experimental drug therapy aiming to decrease the occurrence of pulmonary hypertension, twin pregnancies in which the infant diagnosed with CDH is born first, multiple birth > 2, and placental abnormalities (i.e. anterior placenta praevia, placental abruption). Written informed consent from both parents is required for inclusion. Eligible fetuses will be randomised 1:1 to either PBCC or the standard approach of immediate cord clamping. Study procedures regarding PBCC and immediate cord clamping are explained in the study protocol [9]. Blinding of the allocation arm during intervention is not possible due to the nature of the intervention. Allocation will be stratified by predicted lung size (determined by observed to expected lung-to-head ratio and liver position, graded as mild/moderate/severe lung hypoplasia, measured between 20 and 26 weeks of gestation or at initial visit) and by treatment centre, using variable random permutated block sizes (4-8) [13]. Randomisation and data collection are performed in the electronic data capture system Castor EDC. This electronic database facilitates on-site data entry and ensures concealment of allocation. Security is guaranteed with login names, login codes, and two factor authentication. Only dedicated and trained co-investigators in each centre receive credentials for Castor EDC and are thus allowed to enter data and randomise patients. Patient data are collected until the end of the study period, which is defined as discharge from the tertiary care hospital or death before discharge depending on which occurs first and with a maximum study duration of 6 months.

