#### Secondary outcomes and exploratory outcomes

To limit type I errors, we predefined a limited number of secondary outcomes that will be included in formal statistical analyses. The choice of secondary outcomes was based on clinical relevance and existing literature and includes the following: (1) mortality before discharge from the tertiary care hospital, (2) presence of ≥ 3 criteria for pulmonary hypertension or extracorporeal membrane oxygenation within 24 h after birth, (3) ECMO therapy, (4) duration of supplemental oxygen need, (5) duration of mechanical ventilation, (6) duration of admission to the tertiary care hospital, and the safety parameter (7) postpartum haemorrhage (Table 2). All other secondary outcomes will be considered exploratory outcomes that will not be included in formal statistical testing. Additional to the exploratory outcomes depicted in Table 3, we will collect the following data: echocardiographic confirmation of the presence of pulmonary hypertension requiring therapy on days 7, 14, 21, and 28 and at discharge; the response to iNO defined as one of the following criteria: a decline of 10–20% in pre-postductal SpO_2_ difference, or an increase of 10–20% in PaO_2_, or improvement in haemodynamic parameters meaning 10% increase in mean blood pressure, or a decrease in lactate levels [6]. The number of days needing supplemental oxygen is defined as each calendar day on which the infant required FiO_2_ > 21% for any duration that day. For each calendar day of respiratory support, only the modality with the highest level of support applied on that day will be counted. Causes of death for deceased infants will be summarised in the final report. To objectify the echocardiographic criteria in the primary outcome, we will collect specific echocardiographic parameters in the first 24 h after birth, as depicted in Table 4 [15]. Where possible, the investigator evaluating the echocardiography is blinded to allocation, which will not be feasible in all centres due to limited human resources in routine practice. The first echocardiography including the parameters mentioned in Table 4 will be analysed.

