#### Primary outcome

The effect of PBCC on the primary outcome will be analysed as a complete case analysis in the intention-to-treat population. The main effect of PBCC on pulmonary hypertension will be analysed using the chi-square test. To explore the effect of PBCC on pulmonary hypertension per strata, subgroup analysis per strata (estimated mild/moderate/severe pulmonary hypoplasia) will be performed. An additional sensitivity analysis applying mixed effect models will be conducted to investigate the specific strata. The primary outcome will also be reported as absolute differences in percentages with 95% CI and relative risks with 95% CI to compare the intervention group with the control group (Table 2).

Analysis of the primary outcome will be based on complete cases and by protocol the independent variables in this multivariable analysis cannot be missing as these are required for randomisation. In the rare event that evaluation of the primary outcome has not been performed in the first 24 h, e.g. in the event of mortality before echocardiographic evaluation, the dependent outcome (i.e. pulmonary hypertension) will be missing. To evaluate the robustness of our findings and potential bias by such missing data, we will perform a sensitivity analysis. In this sensitivity analysis, missing values will be imputed by using the ‘worst case’ observed in cases in which the primary outcome was assessed.

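### Excluding every infant whose parents withdraw consent from all analyses discards primary outcomes already recorded, and no sensitivity analysis covers the loss

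*SAP article*

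**What the plan says.** The section Definition of analysis sets opens with "The primary outcome will be analysed in a modified intention to-treat population". This set holds all randomised patients, "independent of actual treatment received, protocol deviations, or post-randomisation ineligibility", with two exceptions. The first is that "patients without a confirmed prenatal diagnosis of CDH will be excluded from all analyses". The second is that "patients whose parents withdraw consent will be excluded from all analyses". The second exception is not limited by the timing of withdrawal, its reason, or the data already held.

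The Primary outcome section under Statistical analyses says that the effect on the primary outcome "will be analysed as a complete case analysis in the intention-to-treat population", without the word modified. It adds one sensitivity analysis for outcomes not evaluated in the first 24 h, in which "missing values will be imputed by using the ‘worst case’ observed in cases in which the primary outcome was assessed".

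Two other sections bear on the point. Randomisation and data collection states that "Blinding of the allocation arm during intervention is not possible due to the nature of the intervention" and that data are collected until discharge from the tertiary hospital or death, up to 6 months. The primary outcome is settled within the first 24 h after birth.

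**The concern.** The primary outcome is known after one day, but parents can withdraw at any time over a follow-up of up to 6 months. As written, a withdrawal in week 8 deletes a primary outcome recorded on day 1. It also deletes that infant's data on mortality, ECMO and postpartum haemorrhage, because the exclusion applies to all analyses.

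Removing randomised infants after the event is harmless to the estimate only if removal is unrelated to outcome or works alike in both arms. Neither can be taken for granted here. The intervention is open, and a family's decision to withdraw may follow the infant's clinical course. If the two arms lose infants of different risk, the comparison is no longer between the groups that were randomised.

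The plan has no check that would reveal this. Its sensitivity analysis concerns outcomes that were never evaluated. An infant excluded from all analyses does not enter that analysis, even when the outcome was evaluated.

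**Working it through.** **Inputs.** From Sample size calculation: control incidence p1 = 0.697, a relative reduction of one third, 80% power, two-sided 5%, at least 140 infants. From Randomisation and data collection: 1:1 allocation. Withdrawal rates are not stated; 2%, 5% and 10% are assumptions.

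**Step 1: reproduce the planned size.** p2 = 0.697 × 2/3 = 0.4647, so the planned difference is d = 0.2323 and the mean proportion is 0.5808. With pooled variance and no continuity correction:

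n per arm = [1.96 √(2 × 0.5808 × 0.4192) + 0.8416 √(0.697 × 0.303 + 0.4647 × 0.5353)]² / 0.2323² = 69.6, rounded up to 70.

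That gives 140 in total, with power 80.2% at 70 per arm. The stated figure is reproduced and contains no allowance for exclusions.

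**Step 2: precision, if both arms lose the same share at random.** Using the same formula with n = 70(1 − w):

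| Share lost, w | n per arm | Power |
|---|---|---|
| 2% | 68.6 | 79.4% |
| 5% | 66.5 | 78.1% |
| 10% | 63.0 | 75.9% |

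This is ordinary loss of information and says nothing about bias.

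**Step 3: bias, if the loss is in one arm and related to outcome.** Suppose there is no true effect, so the risk is 0.697 in both arms. Only the immediate-clamping arm loses a share w, and the withdrawn infants have event risk q. The remaining risk in that arm is (0.697 − wq)/(1 − w), and the spurious difference is 0.697 minus that. The rejection rate of the two-sided 5% test is a normal approximation with 70 against 70(1 − w) infants.

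| w | q | Remaining control risk | Spurious difference, PBCC minus immediate clamping | Rejection rate |
|---|---|---|---|---|
| 5% | 0 | 0.697/0.95 = 0.734 | -3.7 points | 7.6% |
| 5% | 0.697 | 0.697 | 0 | 5.0% |
| 5% | 1 | 0.647/0.95 = 0.681 | +1.6 points | 5.5% |
| 10% | 0 | 0.697/0.90 = 0.774 | -7.7 points | 17.0% |
| 10% | 0.697 | 0.697 | 0 | 5.0% |
| 10% | 1 | 0.597/0.90 = 0.663 | +3.4 points | 7.0% |

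The rows with q = 0 and q = 1 are limits; any real pattern lies between them. With 70 infants in the arm, 5% is 3.5 infants and 10% is 7.

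**The case against.** The strongest reply is that consent governs data use. Whether withdrawal extends to data already collected depends on the consent forms and the protocol, neither of which is shown, and the nine centres lie in seven countries. Full exclusion may be what some consent terms require. Fetuses are randomised, so some withdrawals may come before birth and leave no outcome to keep. This stands as far as it goes: where parents or the consent terms require deletion, the data must go. But the article does not confine the exclusion to those cases.

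The second reply concerns size. No withdrawal rate is given, the limits in the table assume the whole loss falls in one arm, and even then they are small beside 23.2 points. That also stands, and it is why the point is conditional.

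Three stronger readings are tempting, and the document does not support them.

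- A reader might infer two rival primary populations, with the denominator depending on the section followed. Only one set is defined, and its exclusions apply to all analyses. Intention-to-treat in the Primary outcome section is most naturally shorthand for that set.
- A reader might see the first exclusion as contradicting the inclusion of infants who prove ineligible. It is an explicit exception to a general rule. Whether CDH is present is settled before randomisation, so no route to bias has been shown.
- A reader might build a case in which withdrawals make a result significant. With 49/70 against 39/70, removing three PBCC infants who had events gives 49/70 against 36/67, and the uncorrected chi-square p falls from 0.080 to 0.0498. With continuity correction it goes from 0.115 to 0.074 and does not cross 0.05, and the article does not say which version is meant. If the three removed infants were event-free (39/67), the uncorrected p rises to 0.150. The example is selected and does not measure the risk.

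**Conclusion.** The point holds as a defect in a stated rule. The second exclusion discards recorded primary outcomes whatever the timing of withdrawal, in an open trial, and no planned analysis tests the consequence.

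The rule can bias the comparison; nothing shows that it will. Bias requires withdrawal to be related to outcome and to do so differently by arm. Under the assumed one-arm losses and no true effect, the limits are about -3.7 to +1.6 points at 5% and -7.7 to +3.4 points at 10%. The bias is zero if withdrawal is unrelated to outcome, and small if withdrawals are few. The true rate is unknown from the document.

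The difference in label between the two sections is a minor alignment and carries no weight in this conclusion.

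**What to change.** 1. In Definition of analysis sets, change the second exclusion. Data collected up to withdrawal stay in the analysis, and an infant is removed only if the parents ask for data already collected not to be used or the consent terms forbid its use.
2. In the Primary outcome section, include withdrawn infants without a recorded outcome in the existing missing-outcome sensitivity analysis, where consent allows.
3. In the same section, write modified intention-to-treat so that the label matches the definition.

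The cost is a few sentences of SAP text, settled before the data set is locked. No new data are needed. The one real task is to check each centre's consent forms for what they allow after withdrawal; where they differ, the rule will have to follow the local terms.

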### Statistical analyses

#### Patient flow

Figure 1 shows the expected patient flow. A similar figure, completed with numbers per category, will be included in the final report of the trial. We will summarise the reasons why patients are not eligible and the reasons for not including eligible patients if reported. Protocol deviations, defined as deviations in eligibility criteria and patients not being stabilised according to the allocated protocol as set forth in the study protocol, will also be reported.

**Fig. 1 Fig1:**
[figure not shown]
Flowchart of inclusion. CDH, congenital diaphragmatic hernia; ICC, immediate cord clamping; PBCC, physiological-based cord clamping

### Baseline characteristics

All baseline characteristics will be described for each allocation arm of the trial as depicted in Table 1. No formal statistical testing will be performed on baseline characteristics. Continuous data will be reported as mean ± SD or median [IQR] depending on distribution, and categorical data will be reported as counts and percentages.

#### Primary outcome

The effect of PBCC on the primary outcome will be analysed as a complete case analysis in the intention-to-treat population. The main effect of PBCC on pulmonary hypertension will be analysed using the chi-square test. To explore the effect of PBCC on pulmonary hypertension per strata, subgroup analysis per strata (estimated mild/moderate/severe pulmonary hypoplasia) will be performed. An additional sensitivity analysis applying mixed effect models will be conducted to investigate the specific strata. The primary outcome will also be reported as absolute differences in percentages with 95% CI and relative risks with 95% CI to compare the intervention group with the control group (Table 2).

Analysis of the primary outcome will be based on complete cases and by protocol the independent variables in this multivariable analysis cannot be missing as these are required for randomisation. In the rare event that evaluation of the primary outcome has not been performed in the first 24 h, e.g. in the event of mortality before echocardiographic evaluation, the dependent outcome (i.e. pulmonary hypertension) will be missing. To evaluate the robustness of our findings and potential bias by such missing data, we will perform a sensitivity analysis. In this sensitivity analysis, missing values will be imputed by using the ‘worst case’ observed in cases in which the primary outcome was assessed.

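### Randomisation is stratified by hypoplasia grade and centre, but the primary test, risk difference and relative risk are unadjusted, and the same section calls the analysis multivariable.

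*SAP article*

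**What the plan says.** **Design.** The section on randomisation and data collection states "Allocation will be stratified by predicted lung size", graded mild, moderate or severe, and also by treatment centre, in permuted blocks of 4 to 8. The abstract says the same. Nine centres are recruiting.

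**Primary test.** The Primary outcome section under Statistical analyses says "The main effect of PBCC on pulmonary hypertension will be analysed using the chi-square test", and the abstract also names the chi-square test. Neither that section nor Table 2 mentions adjustment of the risk difference or relative risk.

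**Where the strata appear.** They enter through subgroup analyses by grade and through one further model: "An additional sensitivity analysis applying mixed effect models will be conducted to investigate the specific strata". Its terms are not given.

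**The sentence that does not fit.** The next paragraph, on missing data in the primary outcome, says "by protocol the independent variables in this multivariable analysis cannot be missing as these are required for randomisation".

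**The concern.** There are two problems.

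1. **Text.** A two-by-two chi-square test has one independent variable, the arm. The variables needed for randomisation are grade and centre. The missing-data paragraph therefore describes an adjusted model, while the paragraph before it specifies an unadjusted test. The single confirmatory analysis should not leave room for two readings.

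2. **Efficiency.** Stratified allocation removes much of the between-arm variation due to the strata. An unadjusted test still counts that variation as noise. When the strata predict the outcome, its p-value is too large on average and its confidence intervals are too wide. Chance imbalance in grade is also left in the headline estimate. Nine centres by three grades gives 27 cells, and 140/27 is about 5 infants per cell, fewer than a middle-sized block of 6, so many blocks will be incomplete.

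**Working it through.** **Inputs from the SAP article.** On the control rate: "the background incidence of pulmonary hypertension was previously reported at 69.7% in the first week after birth". On the effect: "clinically relevant reduction in pulmonary hypertension incidence of one third", so 0.697 × 2/3 = 0.4647. Two-sided 5%, 80% power, 1:1 allocation, total 140.

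**Step 1: the plan's own figure.** With pooled variance under the null and no continuity correction,

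n per arm = [1.960·√(2·p̄·q̄) + 0.842·√(p1q1 + p2q2)]² / (p1 − p2)²

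Here p̄ = 0.5808, 2p̄q̄ = 0.4869, p1q1 + p2q2 = 0.2112 + 0.2488 = 0.4599 (from unrounded terms), and p1 − p2 = 0.2323.

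n = (1.3677 + 0.5708)² / 0.05398 = 69.6, so 70 per arm and **140 in total**. Power at 70 per arm is 80.2%. The sample size reproduces and matches an uncorrected chi-square test.

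**Step 2: size of the test if balance within grade were perfect.** The outcome variance splits into within-grade and between-grade parts. The chi-square test uses the total; perfectly balanced allocation leaves only the within-grade part. Actual size = 2·[1 − Φ(1.960/√(within/total))]. The rates by grade (mild/moderate/severe) and the 30/40/30% mix are assumptions, chosen so that the overall control rate is about 69.7%.

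- 60/70/79%: within = 0.3·0.24 + 0.4·0.21 + 0.3·0.1659 = 0.2058; total = 0.697·0.303 = 0.2112; ratio 0.974; size 4.7%.
- 50/70/89%: within = 0.3·0.25 + 0.4·0.21 + 0.3·0.0979 = 0.1884; total 0.2112; ratio 0.892; size 3.8%.
- 40/74/94%: within = 0.3·0.24 + 0.4·0.1924 + 0.3·0.0564 = 0.1659; total = 0.698·0.302 = 0.2108; ratio 0.787; size 2.7%.

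With incomplete blocks in 27 cells the balance is imperfect, so the true size should lie between these values and 5%.

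**Step 3: simulation of the design.** Settings: 140 infants, nine centres, blocks of 4, 6 or 8 within grade and centre, overall rates of 69.7% and 46.5%, and a constant odds ratio across grades. Replicates were 8,000 to 20,000 under the null and 6,000 to 15,000 under the alternative. The comparator is a Cochran-Mantel-Haenszel (CMH) test stratified by grade.

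| Assumed control rates | Type I error: chi-square / CMH | Power: chi-square / CMH by grade | Power: CMH over 27 cells |
|---|---|---|---|
| No gradient | 5.1% / 5.0% | 81% / 80% | 78% |
| Weak, 60/70/79% | 5.0% / 5.1% | 81% / 81% | 78% |
| Moderate, 50/70/89% | 4.4% / 5.2% | 81% / 85% | 82% |
| Strong, 40/74/94% | 3.6% / 5.3% | 82% / 89% | 87% |

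Monte Carlo error on a 5% rate with 20,000 replicates is √(0.05·0.95/20,000) = 0.15 points, so the CMH values are compatible with 5%.

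**Step 4: dependence on the effect model.** With a constant relative risk of 2/3 the gain is smaller. At 40/72/92% (mix 25/45/30%) the type I error is about 3.8% against 5.1%, and power is 82% against 85%. At 50/70/89% a separate run gave 4.2% against 4.9%, and 80% against 82%.

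**The case against.** The case for leaving the test alone is reasonable. The sample size was computed for this test, and the test delivers the stated power. Any error is in the safe direction, so it cannot produce a false claim of benefit. A plain two-by-two comparison is transparent, and the planned mixed model and subgroup analyses will show readers whether the result survives adjustment. With a weak gradient or none, nothing is lost.

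Most of this stands, and it limits what can be claimed. A reader might infer any of the following:

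- **The trial is underpowered.** It is not: the uncorrected chi-square had about 80% power or more in every scenario above. The loss is only relative to a better test.
- **The p-value is certainly too conservative.** That requires the strata to be prognostic. The article never says that grade predicts pulmonary hypertension and gives no rates by grade. Its use as stratifier and as the only subgroup factor for the primary outcome makes the link plausible, but it is an inference.
- **Adjustment is absent.** A mixed model is prespecified. It is a sensitivity analysis with unstated terms, however, so it repairs neither the primary p-value nor the reported estimates.

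The objection does not answer the mismatch between the chi-square test and the multivariable sentence, which needs no assumption at all.

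**Conclusion.** The point holds as an internal inconsistency plus an avoidable loss of efficiency. It is not a validity error.

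- **Certain from the text:** the primary test and reported effects do not use the stratification factors, and the section describes the primary analysis in two incompatible ways.
- **Conditional on grade being prognostic:** the test runs at about 4% instead of 5% under moderate to strong assumed gradients. It gives up about 0 to 4 points of power under no to moderate gradients, and up to about 7 under a strong one, relative to a grade-adjusted test.
- **Not affected:** the sample size of 140, the planned 80% power, and protection against false positives.

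The direction is secure and the size is not, because the rates by grade, the grade mix, the centre sizes and the effect model are all assumed. The trade favours adjustment: a three-level stratified test costs at most about 1 point of power if grade is irrelevant.

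**What to change.** 1. Make the primary analysis a CMH test stratified by hypoplasia grade, with Mantel-Haenszel risk difference and relative risk and 95% confidence intervals. An alternative is a logistic model with grade as fixed effect and centre as random intercept, standardised to a marginal risk difference and relative risk. This is a different model that also uses centre. Choose one and name it as primary.
2. Do not stratify over all 27 cells: power falls to about 78% if the strata are weak.
3. Keep the unadjusted chi-square as a sensitivity analysis, and say whether a continuity correction is used. The planned 140 corresponds to no correction; a corrected test would need 156 for 80% power.
4. Rewrite the multivariable sentence in the Primary outcome section, and the test named in the abstract, so that both match the chosen analysis.

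The cost is a dated amendment to the wording before database lock and unblinding. No new data are needed, since both factors are required for randomisation, and the sample size does not change.
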